#### Blinding

Given the nature of the interventions, physicians, nurses, and patients cannot be blinded for the randomized intervention. A blinded adjudication committee will be conducted to confirm each endpoint.

### Study outcomes

#### Primary endpoint

The primary endpoint measure is the percentage of patients without complication at the end of hospitalization in both arms. Complications are defined as: stroke, transient ischemic attack, acute coronary syndrome or elevated troponin, heart failure, arrhythmias or heart conduction disorder, deep vein thrombosis, pulmonary embolism, transfer to intensive care unit, death from any cause, new or progressive radiographic infiltrates, and transfusion-related infections.

#### Secondary endpoints

Secondary endpoints are the of number of PRBC transfused up to 1 month after discharge, cost-effectiveness analysis; the number of patients with grade 3 or 4 bleeding, the number of patients with each complication defined in the primary endpoint, the number of transfusion- related events, number of days with hemoglobin level > 8 g/dL quality of life, duration of neutropenia, the time from randomization to last transfusion, the difference between the hemoglobin level immediately before and the day after transfusion, and the number of transfusion events without respect of the randomization arm. Transfusion-related events are defined as any complication declared by the physician to be related to the transfusion (fever, infection, pulmonary edema, etc.). Quality of life will be assessed using the FACT and QLC30 questionnaires. Neutropenia duration is the time spent with an absolute neutrophil count < 0.5 10^9^/L.

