#### Methodology of the statistical analysis

The number of eligible patients and the number of patients actually included (total and per arm) will be describe in a chart. Qualitative variables will be described as number and percentage, and quantitative variables as number, mean, and standard deviation. Quantitative variables with skewed distribution will be presented as median and interquartile range (25th percentile to 75th percentile). The analysis for the primary endpoint will be conducted in both, intent-to-treat and per-protocol datasets. The difference between randomized arms regarding the primary endpoint will be computed with the corresponding 95 % confidence interval and the appropriate bound will be compared with the non-inferiority margin. All analyses will be stratified by center and reason for hospitalization (blocking factors). If non-inferiority of the experimental arm over the control arm is demonstrated in both the intent-to- treat and per-protocol analyses, superiority tests will eventually be conducted.

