#### Other analysis

Categorical variables will be compared using the χ^2^ or Fisher’s test, as appropriate. Continuous variables will be compared using Student’s *t* test or the Wilcoxon test, as appropriate. The analysis of the overall survival will be adjusted for important stratification and prognostic factors using a multivariate analysis (Cox model). All secondary analyses will be conducted at the bilateral alpha risk of 5 %. Analyses will be performed with SAS version 9.2 (SAS Institute Inc., Cary, NC, USA).

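### Neutropenia duration and time to last transfusion fall under a t test or Wilcoxon rule that scores an early death as a short, favourable value

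*Protocol article*

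**What the plan says.** The Secondary endpoints section of the protocol article names two durations. One is "the time from randomization to last transfusion". The other is neutropenia, defined as follows: "Neutropenia duration is the time spent with an absolute neutrophil count" is below a stated limit. Neither definition says what value a patient has who dies before recovering.

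The Other analysis section gives one rule for quantities of this type: "Continuous variables will be compared using Student’s *t* test or the Wilcoxon test, as appropriate". Its only time-to-event method is reserved for a different outcome: "The analysis of the overall survival will be adjusted for important stratification and prognostic factors using a multivariate analysis (Cox model"). Secondary tests are two-sided at 5%. The Methodology of the statistical analysis section adds: "All analyses will be stratified by center and reason for hospitalization (blocking factors").

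Death is an anticipated outcome. The composite in the Primary endpoint section includes "transfer to intensive care unit, death from any cause". The Data collection and follow-up section ends observation one month after discharge.

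**The concern.** Both durations are read as measures of recovery, where shorter is better, and death stops both clocks. A patient who dies early, still neutropenic and still receiving red cells, has spent few days below the neutrophil limit and has an early last transfusion. A t test or Wilcoxon test on those values cannot tell this patient from one who recovered quickly.

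Administrative follow-up raises a related problem. For a patient still being transfused one month after discharge, the true last transfusion has not been observed, and neither test can represent censoring.

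What is at stake is the reading of two secondary endpoints in a trial meant to show that single-unit transfusion is safe. If one arm had more early deaths, these two results would shift in its favour.

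**Working it through.** **What the plan's figures give.** The article states no expected value for either duration, so there is none to reproduce. Its sample size supplies the arm size and the event rate. With 93% complication-free in both arms, a 10-point margin, 90% power and one-sided 5%:

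n per arm = (1.645 + 1.282)² × 2 × 0.93 × 0.07 / 0.10² ≈ 111.5, so 112.

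This is close to the stated 115 per group. The point below does not depend on it.

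**Deaths the plan allows for.** All complications of every type, death included, are expected in 7% of patients: 0.07 × 230 = 16.1. This covers the hospital stay only. The article gives no separate death rate, so death rates must be assumed.

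**Size of the shift.** Suppose recovery time T has the same distribution in both arms and death at time D cuts it to min(T, D). Then

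mean shift = −(d₂ − d₁) × c, where c = E[max(T − D, 0)]

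Here d₁ and d₂ are the proportions who die in each arm, and c is the average number of days that death removes. The following are assumptions, not in the documents: T lognormal with median 20 days and log-SD 0.4, and D uniform on days 3 to 30. For a given T between 3 and 30, the expected days removed are (T − 3)²/54. Above 30 they are T − 16.5. Averaging over T gives c ≈ 7.6 days.

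For 3% versus 7%: 0.04 × 7.6 ≈ 0.30 day.

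**Simulation.** The same assumptions were used with 115 per arm, 4,000 runs, no true difference in recovery, and an unstratified two-sided Wilcoxon test at 5%. The nominal chance of a significant result in a given direction is 2.5%.

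| Deaths, arm 1 v arm 2 | Expected deaths in total | Shift by formula (days) | Shift simulated (days) | Significant in favour of arm 2 |
|---|---|---|---|---|
| 3% v 3% | 6.9 | 0 | 0.0 | 2.6% |
| 3% v 7% | 11.5 | −0.30 | −0.3 | 4.3% |
| 5% v 10% | 17.3 | −0.38 | −0.4 | 5.7% |
| 5% v 15% | 23.0 | −0.76 | −0.8 | 10.3% |
| 5% v 20% | 28.8 | −1.14 | −1.2 | 17.4% |

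Expected deaths are 115 × (d₁ + d₂). The simulation error at 4.3% is √(0.0425 × 0.9575 / 4000) ≈ 0.3 percentage points, so the rise above 2.5% is not noise.

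**Against the planned rate.** At 3% versus 7%, 11.5 of the 16.1 expected complications would have to be deaths. The three rows below it need more in-hospital deaths than the plan expects complications of all kinds. They apply only if the event rate is well above plan or if deaths after discharge add to the count.

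**The case against.** The strongest reply is that this is read from silence. The rule for continuous variables is general, names neither endpoint, and leaves room for judgement: "test or the Wilcoxon test, as appropriate". Nothing says that a death enters at its shortened value, and a condensed article may leave such rules to a fuller document. That stands as a limit: the method for these endpoints is inferred. It does not remove the point, because the article states a method, that method is the only one on the page that fits, and applied literally it gives the wrong direction for early deaths.

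A second reply is that time spent below a neutrophil limit is an exposure, defined even for a patient who dies. That is correct. The difficulty arises when a shorter exposure is read as better recovery.

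A reader might infer more: that the bias always favours the arm with more deaths, or that a safety problem would be hidden behind apparently faster recovery. The documents support neither. The direction depends on deaths falling early, since a patient who dies late after long neutropenia scores a long duration. Equal deaths produce no bias. A mortality imbalance would also show in the primary composite, in the per-component counts among the secondary endpoints, in recorded vital status and in the survival model. Nor are the comparisons unadjusted, since stratification by center and reason for hospitalization is stated for all analyses.

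**Conclusion.** The point holds in a limited form. The stated rule for continuous variables does not suit two durations that death can cut short. If early deaths differ between arms, both comparisons lean towards the arm with more of them.

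At death rates compatible with the planned 7%, the lean is about 0.3 day, with favourable false positives near 4.3% against 2.5%. It becomes material only with a large imbalance. These sizes rest on the assumed recovery distribution, the assumed window for deaths and an unstratified test; the direction needs only that the extra deaths come before recovery.

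Both endpoints are secondary, and neither enters the non-inferiority decision. This is a worthwhile improvement, not a threat to the trial's main result.

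**What to change.** State the handling of death for both endpoints before data are examined, in one of two ways.

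1. **Time to event.** Analyse time to neutrophil recovery and time to transfusion independence, each with a stated definition. Treat death before recovery as a competing event, censor patients not recovered at the end of follow-up, and use the stratification already planned. Report cumulative incidence by arm.
2. **Worst rank.** Keep the Wilcoxon test, drop the t test option for these two endpoints, rank deaths before recovery as worst, and state where survivors who have not recovered are placed. The result then reflects death and duration together and should be described that way.

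The main cost is a few sentences of analysis text. The first option also changes the estimand, from time spent to time to recovery.

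Data collection needs one check. The Data collection and follow-up section records blood counts and transfusion data daily until discharge, but afterwards names only the number of units. The date of the last transfusion after discharge must be confirmed as collected or added. For patients discharged while still neutropenic, Table 1 lists laboratory tests after discharge only at the one-month visit, so the date of neutrophil recovery may be known only approximately.

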### Statistical method

#### Sample size calculation

The goal of the study is to demonstrate the non-inferiority of the experimental arm compared with the control arm in terms of complication. Based on the hypothesis of 93 % of hospitalizations without severe complication [2] and a non-inferiority margin of 10 % in the single-unit group, a total of 230 subjects (115 per group) should be randomized to provide a study power of 90 % with an alpha risk of 5 %.

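### The 90 % power for 230 patients holds at one-sided 5 %; judged on one bound of a conventional 95 % confidence interval, it is about 84 %

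*Protocol article*

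**What the plan says.** In the Protocol article, Sample size calculation, the planning assumptions are a 93 % rate of hospital stays free of severe complication, a non-inferiority margin of 10 %, and equal groups: "a total of 230 subjects (115 per group) should be randomized to provide a study power of" 90 %, "with an alpha risk of 5" %. The section does not say whether that alpha is one- or two-sided. The Abstract repeats the 230 patients, the 90 % and the 5 %.

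The decision rule is under Methodology of the statistical analysis. The difference between arms is computed with its 95 % "confidence interval and the appropriate bound will be compared with the non-inferiority margin". The sidedness of the interval is not stated there either. On analysis sets the same section says: "The analysis for the primary endpoint will be conducted in both, intent-to-treat and per-protocol datasets". Success in both sets is then named as the condition for going on to superiority tests.

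Only under Other analysis is a test called two-sided, and that sentence covers the secondary analyses.

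**The concern.** A sample size supports its stated power only if it was computed at the error level that the analysis uses. Comparing one bound of a two-sided 95 % interval with a margin is a one-sided 2.5 % test. If 230 was derived at one-sided 5 %, the trial is planned at one level and judged at another.

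Two things are at stake. First, if the strategies are truly equivalent at 93 %, the chance of failing to show non-inferiority is larger than the 10 % that readers are told. Second, with sidedness unstated, the choice between a 90 % and a 95 % interval is not visibly fixed before the data are seen, and a borderline result could turn on it.

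**Working it through.** **Inputs**, all from Sample size calculation unless noted:
- complication-free rate p = 0.93, taken as equal in both arms (no other rate is given)
- margin d = 0.10, read as an absolute difference
- 115 per arm, power 90 %, alpha 5 %
- decision rule: one bound of a 95 % interval (Methodology of the statistical analysis)

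**Formulas** (normal approximation, unpooled variance, equal allocation, no stratification):
- n per arm = (z_alpha + z_0.90)² × 2p(1 − p) / d²
- power = Φ( d / √(2p(1 − p)/n) − z_alpha )

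Here 2p(1 − p) = 2 × 0.93 × 0.07 = 0.1302, and 0.1302 / 0.10² = 13.02. At n = 115 the standard error is √(0.1302/115) = 0.0336, so d / SE = 2.972.

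**Step 1: reproduce the plan's figure, one-sided 5 %.**
- n = (1.645 + 1.282)² × 13.02 = 111.5, so 112 per arm or 224 in total, within 3 % of 230.
- Power at 115 per arm = Φ(2.972 − 1.645) = Φ(1.327) = 90.8 %.

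**Step 2: the decision rule read as a two-sided 95 % interval, one-sided 2.5 %.**
- n = (1.960 + 1.282)² × 13.02 = 136.8, so 137 per arm or 274 in total.
- Power at 115 per arm = Φ(2.972 − 1.960) = Φ(1.012) = 84.4 %.

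**Step 3: exact check.** Enumerating all binomial outcomes with 115 per arm and p = 0.93:

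| Interval | One-sided 5 % | One-sided 2.5 % |
|---|---|---|
| Wald | 89.9 % | 83.7 % |
| Newcombe | 88.5 % | 80.1 % |

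**Step 4: could another method give 230 at one-sided 2.5 %?** None of those tried does. For 90 % power the unpooled formula needs 274, a continuity correction about 314, and the Farrington-Manning variance about 318 (with that variance, the formula gives 77.6 % power at 115 per arm).

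**Step 5: illustration only, both analysis sets required.** This was simulated at one-sided 2.5 % with the Wald interval and 93 % in both arms and both sets. The share excluded from the per-protocol set is an assumption, because the article gives none.

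| Excluded per arm (assumed) | Both sets succeed |
|---|---|
| 5 % | about 81 % |
| 10 % | about 79 % |
| 20 % | about 74 % |

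**The case against.** The strongest reply is that the article never calls the 95 % interval two-sided. It attaches two-sidedness only to the secondary analyses, which leaves room to read the primary test as one-sided at 5 %. If a one-sided 95 % bound was meant, the two sections agree and 230 patients give 90.8 %. This stands as a possibility, so it would be too strong to say that the design cannot have 90 % power. But a 95 % confidence interval for a difference, given without qualification, is conventionally two-sided, and choosing the appropriate bound implies an interval with two. Even on the other reading, the text needs to say so.

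A reader might also infer that non-inferiority requires success in both the intention-to-treat and per-protocol sets, and so put the risk of failure above 20 %. The article does not support that as stated. Success in both sets is written as the gate to superiority testing, not as the criterion for non-inferiority. No exclusion rate is given either, and at an assumed 5 % the joint power is still about 81 %, a failure risk of about 19 %. Nor is the absence of an attrition allowance a defect here, since a condensed article may leave that to the full protocol.

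Finally, this is not a type I error problem. The 95 % rule, read as two-sided, is stricter than the planning alpha, so it does not make a false claim of non-inferiority more likely.

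**Conclusion.** The point holds as a mismatch between the error level of the sample size and that of the decision rule. The stated 230 patients and 90 % power reproduce at one-sided 5 %. Under the conventional reading of the analysis section, power is 84.4 % by formula and 80.1 to 83.7 % by exact enumeration. The risk of missing true non-inferiority is therefore about 16 % by the formula (100 − 84.4 = 15.6 %) rather than 10 %.

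This rests on equal 93 % rates, an absolute 10-point margin, a two-sided interval and an unstratified calculation, whereas the article plans stratified analyses. The joint figures for the two analysis sets are a conditional remark: they apply only if success in both is meant to be required, and only at the assumed exclusion rates.

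**What to change.** Use one alpha, with its sidedness, in both sections. Either:

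1. Keep 230 patients and state that the 95 % interval is two-sided. Restate the power in the Abstract and in Sample size calculation as about 84 % at one-sided 2.5 %, naming the interval method if an exact figure is given.
2. If a one-sided 5 % test was intended, say so in Sample size calculation, and state in Methodology of the statistical analysis that the bound is that of a two-sided 90 % interval (a one-sided 95 % bound). The stated 90 % then stands.

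Also say whether the non-inferiority conclusion itself needs both analysis sets. If it does, report the joint power at the expected exclusion rate.

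The cost is wording only. Option 1 means a slightly less favourable power figure; option 2 means a nominal one-sided error of 5 % instead of 2.5 %. Neither adds patients. Keeping both 90 % power and the two-sided 95 % interval would take 274 patients, 44 more than planned (274 − 230).

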#### Methodology of the statistical analysis

The number of eligible patients and the number of patients actually included (total and per arm) will be describe in a chart. Qualitative variables will be described as number and percentage, and quantitative variables as number, mean, and standard deviation. Quantitative variables with skewed distribution will be presented as median and interquartile range (25th percentile to 75th percentile). The analysis for the primary endpoint will be conducted in both, intent-to-treat and per-protocol datasets. The difference between randomized arms regarding the primary endpoint will be computed with the corresponding 95 % confidence interval and the appropriate bound will be compared with the non-inferiority margin. All analyses will be stratified by center and reason for hospitalization (blocking factors). If non-inferiority of the experimental arm over the control arm is demonstrated in both the intent-to- treat and per-protocol analyses, superiority tests will eventually be conducted.

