**Methods:**

The 1versus2 trial is a randomized trial which will determine if a single-unit transfusion policy is not inferior to a double-unit transfusion policy. The primary endpoint is the incidence of severe complication (grade ≥ 3) defined as stroke, transient ischemic attack, acute coronary syndrome, heart failure, elevated troponin level, intensive care unit transfer, death, new pulmonary infiltrates, and transfusion-related infections during hospital stays. The secondary endpoint is the number of PRBC units transfused per patient per hospital stay. Two hundred and thirty patients will be randomized to receive a single unit or double unit every time the hemoglobin level is less than 8 g/dL. All patients admitted for induction remission chemotherapy, auto-HSCT or allo-HSCT in hematology intensive care units will be eligible for inclusion. Sample size calculation has determined that a patient population of 230 will be required to prove that the 1-unit PRBC strategy is non-inferior to the 2-unit PRBC strategy. Hemoglobin threshold for transfusion is below 8 g/dL. Estimated percentage of complication-free hospital stays is 93 %. In a non-inferiority hypothesis, the number of patients to include is 230 with a power of 90 % and an alpha risk of 5 %.

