### Treatment and study intervention

The study protocol and both arms of randomization are detailed in Fig. 1. Patients randomized in arm A will receive 2 PRBC units if their hemoglobin level is below 8 g/dL during hospitalization and until 1 month after discharge. Patients randomized in arm B (experimental arm) will receive a single PRBC unit if their hemoglobin is below 8 g/dL during hospitalization and until 1 month after discharge. All PRBC units are leukodepleted, and matched according to French policies. Auto-SCT patients will receive irradiated PRBC units and allo-SCT recipients cytomegalovirus (CMV) seronegative irradiated PRBC units [8].

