## Discussion

When and how to transfuse patients in intensive care and hematology units remains a key question. Several meta-analysis have been performed in the context of hemorrhagic syndrome, surgery, coronary syndrome, and septic shock. These studies demonstrated that a restrictive transfusion strategy was associated with a reduction of the number of PRBC transfused, as compared to a liberal strategy. This restrictive transfusion strategy was not inferior to the liberal one in terms of mortality, overall morbidity and myocardial infarction. In hematological malignancies, one pilot prospective randomized trial and one retrospective study have compared bleeding events and the number of blood units used with liberal (trigger 12 g/dL) and restrictive ones (8 g/dL). These studies evidenced a reduction of PRBC units transfused in the restrictive arm [11, 12]. Another way to reduce transfusion side effects and the number of transfusions is to reduce the number of RBP transfused at each transfusion in patients with a potential hematological recovery. The single-unit transfusion strategy is not suitable for patients with chronic anemia due to bone marrow failure or myelodysplastic syndrome without therapy. In a retrospective study, Berger et al. demonstrated a 25 % PRBC unit reduction with a substantial cost saving in the intensive care hematology area with a single-unit transfusion strategy compared to historical two units per transfusion [6]. However, no prospective randomized trials have ever been conducted to compare these two strategies (single-unit versus double-unit transfusion), based on the volume transfused rather than on a hemoglobin level trigger. Another question that arises is the duration of the lower hemoglobin level experienced by the group receiving a single PRBC unit. Here, one can argue that patients may experience greater fatigue in this group with a consequent negative impact on quality of life. Therefore, among secondary endpoints of the study, quality of life will be assessed to compare fatigue between the two arms. The aim of this study is to provide a high level of evidence as to whether a single-unit transfusion in patients with transient bone marrow failure is feasible, safe and reduces patient care costs.

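### If PRBC units per patient are skewed, the stated rules lead to medians and probably a Wilcoxon test, neither of which estimates the saving in units; means with a confidence interval should be specified

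*Protocol article*

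**What the plan says.** The abstract names one secondary outcome: "The secondary endpoint is the number of PRBC units transfused per patient per hospital stay". In the body, the list under Secondary endpoints opens with the "number of PRBC transfused up to 1 month after discharge".

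Under Treatment and study intervention, the arms differ in units per transfusion: "Patients randomized in arm A will receive 2 PRBC units if their hemoglobin level is below 8 g/dL", while arm B patients "will receive a single PRBC unit if their hemoglobin is below 8 g/dL".

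Methodology of the statistical analysis gives one rule for all quantitative variables. The default summary is the count, mean and standard deviation. The exception is: "Quantitative variables with skewed distribution will be presented as median and interquartile range". Other analysis then compares continuous variables by the t "test or the Wilcoxon test, as appropriate". A between-arm difference with a 95 % confidence interval is stated only for the primary endpoint. No effect measure is named for PRBC use.

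The Objective includes a cost reduction, and the Background says the trial is needed to reduce transfusions and hospital cost. The benchmark for the size of the benefit, cited in the Background and again in the Discussion, is a retrospective study that "demonstrated a 25 % PRBC unit reduction with a substantial cost saving".

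**The concern.** A saving in units is a statement about totals, and a total is the number of patients times the mean. Units per patient is bounded at zero, pools induction chemotherapy, autologous and allogeneic transplant patients, and in the body of the protocol runs to one month after discharge. Right skew is the natural expectation. If it appears, the rule replaces the mean by the median, and the Wilcoxon test is the likely companion. A difference in medians cannot be scaled up to units saved, and a Wilcoxon p-value carries no quantity of units.

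The design adds a second difficulty. Adherent arm A patients have totals of 0, 2, 4, 6 and so on, whereas arm B totals can be any whole number. At low use the ratio of the two medians can take only a few widely spaced values.

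At stake is how clearly the benefit of the single-unit policy can be set against the 10-point non-inferiority margin. The primary analysis is not affected.

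**Working it through.** **Inputs from the protocol.** 115 patients per arm (Sample size calculation); two units per transfusion in arm A and one in arm B (Treatment and study intervention); a 25 % reduction as the reference saving (Background, Discussion). The protocol gives no sample size or power for PRBC use, so there is no stated figure for this endpoint to reproduce. The 115 per arm comes from the primary endpoint. With 93 % complication-free in both arms, a margin of 0.10, 90 % power and one-sided 5 %, n = (1.645 + 1.282)² × 2 × 0.93 × 0.07 / 0.10² = 111.5, so 112 per arm, close to 115.

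**Assumed, because the document does not give it.** Arm A mean use of 4, 8 or 16 units, and between-patient spread k = 1.5, 3 or 8 (smaller k means more spread).

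**Model 1.** Arm A total = 2 × NB(μ, k). Arm B total = NB(1.5μ, k). The mean ratio is 1.5μ / 2μ = 0.75, a true saving of exactly 25 %. The median-based saving is 1 − median B / median A, and the mean-based saving is 1 − mean B / mean A. There were 10,000 simulated trials per row.

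| Arm A mean | k | Population medians A, B | Median-based saving ≤ 0 % | Median-based saving ≥ 50 % | Mean-based saving, 5th / 50th / 95th percentile |
|---|---|---|---|---|---|
| 4 | 1.5 | 2, 2 | 67 % | 28 % | 6 / 25 / 40 % |
| 4 | 3 | 4, 2 to 3 | 29 % | 36 % | 9 / 25 / 38 % |
| 4 | 8 | 4, 3 | 8.5 % | 17 % | 12 / 25 / 36 % |
| 8 | 1.5 | 6, 5 | 13 % | 6 % | 8 / 25 / 39 % |
| 8 | 3 | 6, 5 | 16 % | 2 % | 12 / 25 / 36 % |
| 8 | 8 | 8, 6 | 16 % | 0.1 % | 15 / 25 / 34 % |
| 16 | 1.5 | 12, 9 | 9 % | 2 % | 9 / 25 / 38 % |
| 16 | 3 | 14, 11 | 3 % | 0.1 % | 13 / 25 / 35 % |
| 16 | 8 | 16, 11 | 1 % | 0 % | 17 / 25 / 32 % |

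Repeat runs move these frequencies by about one percentage point. In the second row, arm B has exactly half its probability at or below 2, so its population median is anything from 2 to 3 and the implied saving anything from 50 % to 25 %.

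**What the median loses even without an extreme reading.** At an arm A mean of 8 units and k = 3, the mean difference is 8 − 6 = 2 units per patient, or 115 × 2 = 230 units over one arm. The population medians are 6 and 5. That difference of 1 unit (1/6 = 17 %) would scale to 115 units, half the true figure.

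**Imperfect adherence.** With 10 % of arm A transfusions given as one unit, odd totals occur. At an arm A mean of 4 and strong skew, the median-based saving still reads exactly 0 % in 65 % of trials and exactly 50 % in 11 %.

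**Model 2.** Each patient's need is a gamma variable, rounded up to a multiple of two units in arm A and of one unit in arm B, again with a true 25 % saving. At an arm A mean of 4 units, exactly 0 % occurs in 0 to 2 % of trials and exactly 50 % in 0 to 46 %. At 5 units the figures are 8 to 62 % and 2 to 4 %. At 9 units or more they are 0 to 12 % and at most 2 %.

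**The case against.** **The document does not prescribe medians for PRBC use.** A reader might infer that the stated rules necessarily produce medians and a Wilcoxon test. They do not: mean and standard deviation is the default, the median applies only to skewed variables, and the test is chosen as appropriate. This stands, so the point is conditional on skew. Skew is likely for this count but is not stated.

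**Arm A totals need not be even.** That reading requires full adherence, and the protocol plans to count "the number of transfusion events without respect of the randomization arm". This stands, although modest non-adherence did not remove the coarseness at low use.

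**The size rests on assumed usage.** This stands. Extreme readings are frequent at about 4 to 6 units in arm A and uncommon from about 9 or 10. Patients must have a foreseeable transfusion need, which gives no reason to favour the low end. In many scenarios the median-based saving reads 17 to 33 %, so it would be wrong to call the benefit unreadable.

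**Costs do not depend on the median.** A reader might infer that no cost saving could be derived. Data collection and follow-up plans a separate cost-effectiveness analysis with prospectively collected transfusion costs, so that inference fails.

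**This is detail for the analysis plan.** Partly right: an article may leave the effect measure for a secondary endpoint to a fuller document. But this article does state a rule, and the rule drops the mean in just the case that is likely here. An analysis plan that followed it would inherit the problem.

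No general loss of power from Wilcoxon is claimed. It was lower than the t test in skewed Model 1 cases (23 % v 52 % at a mean of 4) and about equal in Model 2 (91 % v 89 % at a mean of 6).

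**Conclusion.** The point holds in conditional form. If PRBC units are skewed, the stated summary and the likely test do not estimate the saving in units, and that is true at every level of use. The added coarseness from steps of two against steps of one depends on usage. Under the negative binomial assumption, a real 25 % saving would read as zero or negative in roughly 8 to 67 % of trials at an arm A mean of 4 units, falling to 13 to 16 % at 8 and 1 to 9 % at 16. The alternative model gives generally smaller and less regular effects. The mean-based saving is centred on 25 % in every Model 1 scenario, with 5th to 95th percentiles from 6–40 % at worst to 17–32 % at best among the rows shown. The change is worth making before analysis. It bears on the main secondary result, not on the non-inferiority conclusion.

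**What to change.** In Methodology of the statistical analysis and Other analysis, add that PRBC units per patient are reported as arithmetic means per arm whatever the skew. Give the mean difference and the ratio of means, each with a 95 % confidence interval, from a bootstrap or a count model with robust variance, stratified by center and reason for hospitalization as already planned. Keep median, interquartile range and Wilcoxon as supplementary. State which counting window the estimate uses, since the abstract refers to the hospital stay and the endpoint list to one month after discharge.

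The cost is a few lines of wording, with no new data and no additional patients.
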